**Interventions:**

Participants are assigned to: (1) emergency total ECLS, with initiation as soon as possible after randomization and within 60 min of the emergency call, or (2) standard ACLS with rescue ECLS, in which at least 15 min of standard ACLS is provided in the ED before ECLS is considered. Both groups receive immediate coronary angiography and percutaneous coronary intervention (PCI) when indicated, and active LV unloading is recommended according to prespecified criteria.

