**Fig. 1 Fig1:**
[figure not shown]
Study flowchart. Before arriving at ED, the eligibility of OHCA patients will be evaluated by the OHCA response team of the receiving hospital, based on on-scene information provided by EMS. For eligible OHCA patients, randomization will be completed within 5 min of arrival at ED. After CT imaging, patients of first enrollment will be checked again if any exclusion criteria are met. Only patients who received early coronary angiography and/or intervention will be included in the final analysis. ACLS: advanced cardiovascular life support; CCL: cardiac catheterization laboratory; CPC: cerebral performance category; CPR: cardiopulmonary resuscitation; CT: computed tomography; ECLS: extracorporeal life support; ED: emergency department; EKG: electrocardiography; EMS: emergency medical services; mRS: modified Rankin scale; OHCA: out-of-hospital cardiac arrest; ROSC: return of spontaneous circulation; ECG: echocardiography

Randomization is performed immediately upon ED arrival (target: within 5 min) for patients meeting inclusion criteria and experiencing refractory cardiac arrest (defined as ongoing CPR on arrival). Patients with stable ROSC before randomization (defined as sustained pulse with systolic BP ≥ 90 mmHg without ongoing chest compressions for ≥ 2 min) are not randomized and proceed directly to coronary angiography.

Patients with unstable ROSC defined as: (1) return of pulse but requiring ongoing chest compressions, (2) recurrent VF/VT requiring repeated defibrillation, (3) persistent profound hypotension with systolic BP < 90 mmHg or mean BP < 60 mmHg despite vasopressor support, or (4) intermittent epinephrine injection to maintain the heart beating are eligible for randomization."

A computerized randomization list is provided by the National Taiwan University Hospital Clinical Trial Center by a software app (REDCAP). The randomization is in 1:1 ratio, stratified by participant hospitals, with a permuted block of 4. In-hospital randomization is conducted by OHCA response team coordinators immediately after the eligible patients arrive at ED. The randomization codes will be maintained by the National Taiwan University Hospital Clinical Trial Center and monitored by the Data Safety Monitoring Committee. The EMS teams and intensivists in the cardiac intensive care unit (ICU) will be blinded to the study group assignment and follow the institutional standards for post-cardiac arrest care.

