#### Intervention—ECMO initiation

After randomization, if the enrolled patient has stable ROSC before initiating ECMO, he/she will be transferred to the cardiac catheterization laboratory (CCL) without ECMO support. The indications for ECMO include no ROSC or unstable ROSC (persistent or recurrent VF or pVT, profound cardiogenic shock with systolic blood pressure (BP) < 90 mmHg or mean BP < 60 mmHg despite intense inotropic support (bolus of epinephrine > 3 bolus), or persistent hypoxia with arterial oxygen saturation (SaO2) < 90% despite maximal ventilation support). The femoral artery and vein access will be cannulated under ultrasound guidance. ECMO would be deemed futile if more than one discontinuation criterion suggesting ineffective resuscitation (end-tidal carbon dioxide < 10 mmHg, partial pressure of oxygen in arterial blood < 50 mmHg or oxygen saturation < 85%, or serum lactate > 20 mmol/L) has been met.

However, if unstable ROSC persists as defined above, ECMO is initiated according to the randomization arm protocol. For the emergency total ECLS group (Fig. 1), the veno-arterial ECMO (VA-ECMO) will be initiated within 15 min after randomization. For standard ACLS with the recue ECMO group, patients will receive 15 min of ACLS at ED first. If there is no stable ROSC, the futility of ECLS would be reevaluated. Therefore, the recue VA-ECMO should be initiated after 15 min since randomization.

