### Statistical analysis

#### Sample size rationale

The trial is designed to demonstrate a treatment effect on the primary endpoint. Accepting a power of 80% and a level of significance of 5%, the sample size is calculated using a two-sided chi-square test. In reference to published multicenter trials, we estimate a 30-day neurologically favorable survival of 25% and 12% in the emergency total ECLS group and the standard ACLS with rescue ECMO group, respectively. Assuming a 10% dropout rate, we plan to enroll 186 participants per arm (roughly 200). No interim analysis is planned. If interim analysis is deemed necessary determined by Consortium committee, we will conduct one interim analysis 1 year after enrollment, and the statistical testing will be adjusted to this accordingly. The flowchart of intention to treatment and per protocol are attached in supplement.

All patients enrolled in the study will be analyzed primarily on an intention-to-treat basis. Continuous variables will be reported as mean ± standard deviation or median with interquartile range. Categorical variables will be presented as frequency. A logistic regression model with the stratification variable (center) will be conducted to evaluate the primary efficacy endpoint by treatment group. Odds ratios are to be calculated as effect estimates with 95% confidence intervals. Patients whose primary outcome cannot be assessed will be regarded as failures.

Per-protocol analysis, which only includes patients who adhere to the allocated protocol, will be performed to minimize the impact of non-adherence or deviations from the strict protocol.

For patients randomized to the total ECLS group, if ECPR is not required due to stable ROSC at ED or ECMO is initiated after 20 min since arriving at ED or after 60 min since emergency calls, they would be excluded from per-protocol analysis. Similarly, for patients randomized to the standard ACLS with rescue ECMO group, if ECMO is initiated within 20 min of arriving at the ED or within 60 min of emergency calls, they would be considered crossover and excluded from per-protocol analysis.

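### The per-protocol time limits use a different clock from the assigned strategies, and the 60-minute-from-call limit excludes control patients treated as assigned and selects the arms in opposite directions on call-to-ED time

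*Protocol article*

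**What the plan says.** All places are in the protocol article.

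**Assigned strategies.** The section Intervention—ECMO initiation counts from randomization. In the total ECLS arm "the veno-arterial ECMO (VA-ECMO) will be initiated within 15 min after randomization". In the standard arm 15 min of ACLS come first, and then "the recue VA-ECMO should be initiated after 15 min since randomization". The legend of Fig. 1 adds that "randomization will be completed within 5 min of arrival at ED".

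**A second statement for the ECLS arm.** The abstract (Interventions) describes that strategy as ECLS "with initiation as soon as possible after randomization and within 60 min of the emergency call". Table 3 likewise lists 60 min from the call as the allowed limit. Neither place gives the standard arm a minimum time from the call.

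**Per-protocol set** (Statistical analysis, under Sample size rationale).
- Total ECLS arm: where "ECMO is initiated after 20 min since arriving at ED or after 60 min since emergency calls, they would be excluded from per-protocol analysis". Patients are also excluded "if ECPR is not required due to stable ROSC at ED".
- Standard arm: "if ECMO is initiated within 20 min of arriving at the ED or within 60 min of emergency calls, they would be considered crossover", and they are excluded. No stable-ROSC exclusion is stated for this arm.

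Intention-to-treat is the primary analysis, and the per-protocol analysis is additional.

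**The concern.** A per-protocol set should keep patients who received what they were assigned. Here the assignment runs on one clock and the adherence check on two others. Call-to-ECMO time is largely call-to-ED time, which is fixed before randomization and has nothing to do with adherence after it. The subgroup list makes call-to-ED time a subgroup factor on the ground that low-flow time is critical to neurological outcome.

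Because the 60-min limit points in opposite directions in the two arms, it tends to keep early-arriving ECLS patients and, among controls who receive ECMO, late-arriving ones. The per-protocol comparison then contains a baseline imbalance created by its own inclusion rule. In an open-label trial, where this analysis will be read as a check on non-adherence, that matters.

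**Working it through.** The plan gives no figure for the per-protocol set, so there is none to reproduce. Write T for call-to-ED time and a for time from ED arrival to ECMO, both in minutes.

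**1. The rule as written**
- ECLS arm kept if a ≤ 20 and T + a ≤ 60.
- Cannulated control kept if a > 20 and T + a > 60.
- Control never given ECMO: kept whatever T is.

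**2. Where the 60-min limit bites**

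| Arm | a | Kept only if |
|---|---|---|
| ECLS | 20 (5 to randomize + 15) | T ≤ 60 − 20 = 40 |
| ECLS | 10 | T ≤ 60 − 10 = 50 |
| Control | 25 | T > 60 − 25 = 35 |
| Control | 30 | T > 60 − 30 = 30 |

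Table 1 admits estimated T below 60 min, and the section on EMS in the Taipei metropolitan area expects a mean of about 40–60 min. The limit will therefore bind often.

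**3. Individual cases**
- Control: arrival at 30, randomization at 32, ECMO at 57. ECMO starts 57 − 32 = 25 min after randomization and 57 − 30 = 27 min after arrival. This fits the intervention section, but 57 ≤ 60 makes the patient a crossover.
- ECLS: arrival at 47, randomization at 50, ECMO at 62. ECMO starts 62 − 50 = 12 min after randomization and 15 min after arrival. This is on protocol under the intervention section, but off protocol under the abstract and Table 3, and excluded because 62 > 60.

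**4. Size of the selection (the distributions are assumptions)**

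T normal with SD 10, truncated to 15–60; randomization 0.5–5 min after arrival; ECMO about 12 min (ECLS) or 24 min (control) after randomization:

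| Mean T before truncation | ECLS kept | Cannulated controls kept | Gap in mean T |
|---|---|---|---|
| 40 | 66% | 75% | 7.8 |
| 45 | 52% | 87% | 7.7 (38.1 vs 45.8) |
| 50 | 38% | 94% | 8.1 |

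Other choices for the spread of the delays put the gap at about 8–9 min.

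**5. Effect on the odds ratio when treatment does nothing**

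If the odds of a good outcome are multiplied by r for each 10 min of T, a gap of 8 min gives roughly OR = r^(−0.8).
- r = 0.8 (20% fall): 0.8^(−0.8) = 1.20.
- r = 0.6 (40% fall): 0.6^(−0.8) = 1.50.

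Simulating the full rule gives about 1.2–1.55. If half of controls are never cannulated, and so always kept, it gives 1.13–1.50.

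**6. Sensitivity**

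A second set-up used SD 8, a uniform on 10–20 (ECLS) or 20–40 (control), and mean T 35–50. With an odds ratio of 0.95 per minute (0.95^10 ≈ 0.60 per 10 min) the null OR is 1.28–1.46. Over 0.93–0.97 per minute it is 1.16–1.69. When adherence is judged only from randomization, mean T is equal in the two arms and the null OR is 1.00.

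**7. The stable-ROSC exclusion**

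Assume equal stable-ROSC frequency in both arms, 15% good outcome without it and 40–50% with it, mean T 45, and the same 20–40% fall. The null OR, excluding stable ROSC from the ECLS arm only, becomes:

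| Stable ROSC | Null OR |
|---|---|
| 0% | 1.19–1.50 |
| 5% | 1.02–1.31 |
| 10% | 0.88–1.17 |
| 15% | 0.77–1.05 |
| 20% | 0.69–0.97 |

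**The case against.** Five things can be said for the plan.

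- **The ECLS-arm limit has a basis.** The abstract and Table 3 put 60 min from the call inside the ECLS strategy. A reader might infer that the rule drops patients treated as assigned in both arms. The documents do not support that: the ECLS patient at 62 min is on protocol in one section and off protocol in two other places. This objection stands, and it turns the ECLS side into a contradiction to be reconciled. It does not help the control side, where no such statement exists.
- **The 20-min-from-arrival limit is reasonable.** It equals 5 min to randomize plus 15 min, so it agrees with the intervention section when randomization takes the full 5 min.
- **Only cannulated controls are selected for late arrival.** Controls never given ECMO stay in. This stands. It weakens the imbalance but does not remove it, as the 1.13–1.50 range shows.
- **The direction is not settled.** A reader might infer that the per-protocol analysis will show a false ECLS advantage. The one-sided stable-ROSC exclusion plausibly removes good-prognosis patients from the ECLS arm alone, and under the assumptions in step 7 it can cancel or reverse the timing bias. This stands.
- **The analysis is supplementary.** Intention-to-treat is primary, and a per-protocol flowchart is in a supplement not available here. This limits the weight of the point, but the article states the exclusion rule itself in full.

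**Conclusion.** The point holds for the mismatch of clocks and for the control-arm limit of 60 min from the call. That limit has no counterpart in the assigned strategy and labels correctly treated controls as crossovers. For the ECLS arm, the finding is that the timing statements conflict.

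The timing rule taken alone favours ECLS: about 8–9 min difference in retained call-to-ED time and a null OR of about 1.2–1.55 (1.13–1.50 with half of controls never cannulated). This rests on an assumed call-to-ED mean of 40–50 min with SD 10, assumed ECMO delays, and an assumed 20–40% fall in odds per 10 min. The documents give neither a spread for call-to-ED time nor a slope for outcome.

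It should not be read as the net bias of the per-protocol analysis, because the stable-ROSC exclusion may act in the opposite direction. Confidence is high on the clock mismatch and the control limit, and low on the net direction. The primary result is not affected. The definition should be corrected, but the point does not threaten the trial's main conclusion.

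**What to change.** 1. Remove the 60-min-from-call condition from the control arm's per-protocol definition, and judge adherence there on the same clock as the assigned strategy, namely randomization.
2. Reconcile the ECLS-arm timing in the abstract, the intervention section, the per-protocol paragraph and Table 3, and use the reconciled rule for adherence. Which limit applies is for the investigators to decide.
3. Treat stable ROSC before ECMO in the same way in both arms.
4. Adjust the per-protocol model for call-to-ED time, which the planned subgroup analysis already needs.
5. State that the per-protocol result is supplementary, since any such set still conditions on events after randomization.

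The cost is a change of wording, best made before outcomes are analysed. The present rules already need the call, arrival and ECMO-start times, and the electronic randomization should supply the randomization time.

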### Cost-effectiveness analysis

A comprehensive cost-effectiveness analysis will be conducted from both healthcare system and societal perspectives. Data collection includes: (1) Direct medical costs**:** ECMO equipment and disposables, catheterization laboratory procedures, ICU and hospital stay, medications, rehabilitation services, and (2) Indirect costs: Lost productivity, caregiver burden (collected via structured surveys). The Outcomes of Quality-adjusted life years (QALYs) are calculated using EQ-5D-5L assessments at discharge, 3 months, 6 months, and 1 year.

Incremental cost-effectiveness ratio (ICER) will be calculated as cost per QALY gained. Sensitivity analyses will examine uncertainty in cost and outcome estimates. A willingness-to-pay threshold consistent with Taiwan's healthcare context (approximately $50,000–100,000 USD per QALY) will be used for interpretation."

### Ethical considerations

According to the Taiwan Medical Care Act, Chapter 4, Article 63 and Article 64 (latest version, June 28, 2023), written informed consent about the reason for the procedure, success rate, risk, and possible side effects of surgical operation and invasive intervention treatment must be obtained from the patient or, when underage or incapacitated, from a legal representative, spouse, or related relative. However, the provisions do not apply to medical emergencies. Informed consent could be waived for enrollment of eligible subjects in the critical emergency. Instead, a deferred consent will be sought whenever the emergency condition is under control. In ethical consideration, the study is conducted in accordance with the Declaration of Helsinki and is approved by the Institutional Review Board on the ethics of human investigation of each participating hospital.

## Discussion

Successful resuscitation of individuals experiencing OHCA requires a coordinated set of timely actions termed the “Chain of”Survival”—early recognition and activation of the emergency response system, early CPR, rapid defibrillation, and early advanced life support [22]. Our country has developed a well-organized EMS system, launching a series of optimization initiatives over the past decades, including prehospital 12-lead electrocardiography in 2012, public-access defibrillators in 2013, and dispatcher-assisted CPR implementation in 2013 [23]. According to a chronological, community-wide observational study in Taipei, 12.6% patients with non-traumatic OHCA initially presented with a shockable rhythm. With sequential implementations of optimizing initiatives, the rate of bystander CPR significantly increased from 32.6% in 2010 to 62.8% in 2017 (P < 0.001) [19]. Furthermore, each participating institution in this trial is capable of 24/7 ECMO cannulation and transportation, cardiac catheterization, and cardiac surgery, performing > 10 ECPR procedures per year. Expedited application of ECPR is only possible under highly controlled coordination and well-balanced strengthening of each link in the Chain of Survival. Considering the estimated distance from ECPR centers and EMS response times, we adopt the’load and go’ ECPR strategy for refractory shockable OHCA in this trial [24]. Because of the conflicting results from the 3 RCTs, critical appraisals of individual studies have addressed the differences in the study designs and offered insightful interpretations of the conclusions [11–13, 24]. Therefore, our study is designed to address the key disputable issues of the 3 RCTs, aiming to provide complementary data to support the use of ECPR for refractory shockable OHCA and to evaluate the cost-effectiveness of expedited application of ECPR (Table 3). We also extend the duration of call to ED to 60 min, thus it may lead to longer low flow time.

**Table 3 Tab3:** Study characteristics of published randomized controlled trials and the ECLS-OHCA trial

	**ARREST**^**11, 17**^	**Prague OHCA**^**12, 17**^	**INCEPTION**^**13, 17**^	**ECLS-OHCA**
Refractory OHCA	Three defibrillation shocks	5 min of advanced cardiac life support	15 min of advanced life support	Cardiac arrest on arrival at ED
Witnessed with bystander CPR	±	+	+	+
Initial rhythm	VF or VT	All rhythms	VF or VT	VF or VT
Intervention	ECPR and early revascularization	Invasive bundle	ECPR	Expedited ECPR and early revascularization
Comparator	CCPR and early revascularization	CCPR with encouraged immediate invasive assessment	CCPR	CCPR with rescue ECLS and early revascularization
Randomization	In-hospital	Prehospital	Prehospital	In-hospital
Primary endpoint	Survival to hospital discharge	180-day neurological favorable survival	30-day neurological favorable survival	30-day neurological favorable survival
EMS response time (minutes, mean ± SD)	6.5 ± 2.4	8.9 ± 3.0	8 ± 4	6.4 ± 3.3 (estimate)
Time from emergency calls to ECLS (minutes, mean ± SD)	59 ± 28	62.0 ± 11.3	74.7 ± 18.2	≤ 45 (estimate), within 60 min is allowed
Time from randomization to ECLS initiation (minutes, mean ± SD)	12 ± 6	NR	NR	≤ 15 (estimate)

CCPR, conventional cardiopulmonary resuscitation; CPR, cardiopulmonary resuscitation; ECLS, extracorporeal life support; ECPR, extracorporeal cardiopulmonary resuscitation; ED, emergency department; EMS, emergency medical service; NR, not reported; OHCA, out-of-hospital cardiac arrest; SD, standard deviation; VF, ventricular fibrillation; VT, ventricular tachycardia

Outcomes of OHCA would not be optimized without addressing treatment of underlying causes and post-cardiac arrest care. Because acute coronary syndrome (ACS) is the most common reversible underlying cause in patients with shockable OHCA, as might be anticipated, patients with refractory shockable OHCA are more likely to be associated with more severe coronary lesions, e.g. left main involvement and acute occlusion of left anterior descending artery [25]. Due to the similarly time-sensitive nature of ischemic myocardial injury, early reperfusion is recommended in patients with ACS. Immediate coronary angiography (CAG) and primary percutaneous coronary intervention (PCI) after cardiac arrest is reasonable for patients with shock, electrical instability, signs of significant ongoing myocardial damage, or ongoing ischemia [14]. In patients with refractory shockable OHCA, ECMO-assisted intra-arrest PCI without continuing chest compressions has been proved feasible [26]. In high-volume ECMO centers, a treatment algorithm of ECPR-facilitated PCI for refractory shockable OHCA has been advocated. The Minnesota Resuscitation Consortium incorporated ECMO for hemodynamic stabilization and emergent PCI for coronary reperfusion in the clinical pathway of refractory shockable OHCA and reported improved hospital survival and survival with good neurological outcome of 55% and 50%, respectively [27].

When peripheral ECLS is used in cases with poor LV function, the increased LV afterload owing to the retrograde flow can lead to LV distension, impaired coronary perfusion, arrhythmias, pulmonary congestion, LV thrombus formation, etc., which might compromise the myocardial recovery [28]. Research has indicated that early active LV unloading during ECMO support improves survival in patients with cardiogenic shock [29]. Myocardial stunning frequently occurs after cardiac arrest. For patients with initial shockable rhythm, myocardial dysfunction may be further aggravated by the presence of acute coronary syndrome [30].

Concomitant LV unloading with ECPR was reported to be associated with favorable outcomes in patients with refractory cardiac arrest [31]. Practical guidelines for the post-cardiac arrest care in ECPR patients have incorporated LV unloading as one of the focused topics [32]. While none of the 3 RCTs had discussed their managements of LV distension complication in ECPR patients, our study will adopt novel LV unloading strategies under prespecified selection criteria.

## Conclusion

The ECLS-OHCA trial is a multicenter, open-label, interventional randomized clinical trial conducted in a metropolitan area with a well-developed EMS system and densely distributed healthcare facilities. All participating institutions are expert ECMO centers capable of 24/7 ECMO cannulation and transportation, allowing for expedited application of ECPR in eligible candidates with refractory shockable OHCA. Patients without identified noncardiac causes of OHCA will receive immediate CAG and primary PCI if indicated. Institutional protocols of post-cardiac arrest care will adhere to established recommendations from the latest guidelines. Active LV unloading is suggested in cases demonstrating the signs of LV overload. Our trial aims to provide complementary evidence supporting the use of ECPR in refractory shockable OHCA and to assess the cost-effectiveness of its early implementation.

